## Methods/design

This study is a multicenter randomized controlled non-inferiority trial in which treatment with low-dose (10–20 mg nightly) AM is compared with the golden standard, CBT-I. Eligible consenting patients are randomized to 1) CBT-I or 2) low dose of AM, both for a period of 12 weeks in a ratio of 1:1. Patients are followed up to 12 months post treatment (thus 15 months post randomization). The study is implemented in regular care of the outpatient clinic of the departments of neurology (sleep-wake center) and departments of medical psychology of the participating Dutch hospitals (see Fig. 1 for a flow chart).

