### Sample size

We hypothesize that the effect of low-dose AM at 12 weeks is non-inferior to the golden standard CBT-I. A low-dose AM will be considered non-inferior to CBT if the mean post treatment ISI total score does not exceed that of the CBT-I group by more than 4 points, i.e., 50% of the minimum clinical significant difference reported following CBT-I. The standard deviation of the ISI in our study is assumed 4.4 [61]. Sample size determination following the recommendations outlined in Tamayo-Sarver et al. [62] using a one-tailed test and a 5% significance level showed that 84 participants in each group will provide adequate power (90%) to reject the null hypothesis that the ISI change produced by low-dose amitriptyline is not similar to those produced by CBT-I. The dropout rate is estimated to be 13% [41]. Hence, 190 participants in total will be included.

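### At the stated 13% dropout, 190 randomised patients leave about 165 completers, slightly fewer than the 168 (84 per group) that the sample size section calls for

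*Protocol article*

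**What the plan says.** All the figures stand in one paragraph of the protocol article, under Sample size. It gives 84 per group as the number needed for 90% power, "using a one-tailed test and a 5% significance level". Non-inferiority requires that the mean ISI score on amitriptyline "does not exceed that of the CBT-I group by more than 4 points", and the assumed SD is 4.4. The paragraph ends: "The dropout rate is estimated to be 13% [41]. Hence, 190 participants in total will be included".

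The Methods/design section fixes the allocation, "both for a period of 12 weeks in a ratio of 1:1", so the number required before any loss is 2 × 84 = 168. The total of 190 is repeated as the target in the Abstract and under Trial status. No section states how the dropout allowance was applied, and none corrects the figure.

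**The concern.** The paragraph presents 190 as the consequence of 84 per group and 13% dropout. If 190 is the right number to randomise, 84 per group should remain after 13% have left, and they do not. The match with 168 × 1.13 suggests that 13% of the required number was added on. What is needed is the total from which 13% can be lost.

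What is at stake is a headline design figure that does not follow from its own inputs. Readers use the target, the dropout rate and the number of completers together to judge whether recruitment and retention were adequate. As written, a trial that recruits exactly to target and loses exactly the predicted share would still miss its stated number of completers.

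**Working it through.** **Inputs** (Sample size section unless noted)
- Required per group: 84; two equal groups (Methods/design), so 168 in total.
- Dropout: 13%.
- Stated total to include: 190.
- Margin 4 ISI points, SD 4.4, one-sided 5%, target power 90%.

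**Step 1: reproduce the stated total.** Multiplying by (1 + dropout):
- 168 × 1.13 = 189.84, rounded up to 190.
- 84 × 1.13 = 94.92, rounded up to 95 per group, 190 in total.

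Both routes give exactly 190. The article does not write this formula down; it is inferred from the match.

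**Step 2: the allowance that retains 84 per group.** Dividing by (1 − dropout):
- 168 / 0.87 = 193.1.
- 84 / 0.87 = 96.55, rounded up to 97 per group, 194 in total.
- Difference: 194 − 190 = 4 patients, and 4 / 190 = 2.1%.

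**Step 3: what 190 delivers at 13% dropout.**
- 190 × 0.87 = 165.3 completers; 95 × 0.87 = 82.65 per group.
- Shortfall: 168 − 165.3 = 2.7 in total; 84 − 82.65 = 1.35 per group.

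**Step 4: the dropout rate that 190 can absorb.**
- 1 − 168 / 190 = 11.6%.

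Steps 3 and 4 do not depend on how 190 was obtained.

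**Step 5: effect on power, using the stated inputs.** Normal approximation, assuming no true difference between the arms (the article does not state one): power = Φ(4 / (4.4 × √(2/n)) − 1.645), with n per group.
- n = 84: 4 / 0.679 = 5.89; Φ(4.25), above 99.9%.
- n = 82.65: 4 / 0.684 = 5.84; Φ(4.20), above 99.9%.

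On these inputs the shortfall does not bring power anywhere near 90%.

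**Step 6: why power is so high.** With the same inputs, the number needed for 90% power is 2 × (4.4 × (1.645 + 1.282) / 4)² = 20.7, or 21 per group. The stated 84 therefore does not follow from the stated margin and SD. That is a separate question, but it limits what can be said here about power.

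**The case against.** The strongest reply is that nothing practical depends on this. The difference is 4 patients in 190, and the 13% is itself an estimate that could easily be wrong by more than the 1.4 points separating it from 11.6%. The primary analysis under Statistical analysis keeps every randomised patient and imputes missing week-12 ISI scores, so the analysis set is 190 and not 165. The ANCOVA also adjusts for baseline ISI. If 4.4 is an unadjusted SD (an assumption, since the article does not say), a correlation r between baseline and week 12 with 1 − r² = 165.3 / 168 = 0.984, that is r of about 0.13, would offset the lost patients.

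Most of this stands, and it is why the point is minor. It does not make the sentence correct. Imputation keeps patients in the analysis but does not recover all the information in an unobserved outcome. The Sample size section itself treats dropout as a loss to be made good. The planned per-protocol analysis keeps only patients who received enough of their assigned treatment, so numbers do fall there.

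A reader might go further and infer that the trial falls below 90% power. The article does not support that. A figure just under 90% appears only if the relevant distance is 2 points instead of 4, either as a 2-point margin or as an assumed true difference of 2 points favouring CBT-I. Each gives 83 per group and so comes close to 84, but the article states neither, and both the Sample size and Statistical analysis sections fix the margin at 4. Even on that unstated basis the loss is about 0.4 percentage points (90.3% at 84 per group, 89.9% at 82.65, normal approximation).

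A reader might also take the × 1.13 step as documented. It is a well-supported inference and no more.

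**Conclusion.** The point holds as a small arithmetic correction. Three figures in one paragraph, namely 84 per group, 13% dropout and 190 in total, do not fit together: 190 leaves about 165 completers, 2.7 short of 168, and 194 would be needed to retain 84 per group. This rests only on reading 13% as the share of randomised patients lost, applied equally to both arms. The likely cause, multiplying by 1.13, is inferred.

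There is no demonstrated loss of adequate power. On the stated margin and SD, with no true difference, power exceeds 99.9% with or without the shortfall. The design, the analysis and the decision rule are unaffected. The point also does not imply that 84 is itself sound; that number needs its own justification.

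**What to change.** Keep 190 and replace the closing sentence of the Sample size section with one of two statements: that 190 randomised gives about 165 completers (82 to 83 per group) at 13% dropout, or that 190 retains 84 per group provided dropout does not exceed 11.6%. The first is preferable because it leaves the cited dropout estimate as it is. Do not add a 2-point margin, or a power figure based on one, since that would contradict the 4-point decision rule.

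Make the change in the same revision that explains how 84 per group follows from the stated margin and SD, because the dropout sentence depends on that number. The cost is one sentence. No extra patients are needed, and the total of 190 in the Abstract and under Trial status can stay.

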### Statistical analysis

Demographic and clinical characteristics (e.g., age, gender, medical condition, preference and type of insomnia) and primary and secondary outcomes at baseline (e.g., sleep efficiency, emotional complaints) will be presented in means (standard deviations) and numbers (percentages) depending on their distribution.

The null hypothesis states that there is a difference in mean scores on the primary outcome between the treatment groups; the alternative hypothesis is that the difference in mean scores on the primary outcome measure does not differ by more than the non-inferiority margin. The primary analysis will be conducted according to intention-to-treat, i.e., all randomized patients are included and are analyzed in their randomly assigned treatment group. Outcomes that are based on measurements at multiple time points, i.e., weeks 6 and 12, are analyzed using mixed linear models. Mixed linear models can handle the presence of missing data without the need for imputation and still provide valid estimates of treatment effects.

The primary outcome for analysis is the mean subjective insomnia severity as assessed using the ISI at week 12. To test for the difference between the two treatment groups, the primary outcome of ISI score at week 12 will be analyzed using analysis of covariance (ANCOVA) with treatment group (amitriptyline or CBT-I) as the independent variable and the baseline value as a covariate. We will check for violations of necessary assumptions of ANCOVA (normality, homogeneity of variance and random independent samples). We will calculate a one-sided 95% confidence interval around the mean difference in the primary outcome between the treatment groups to determine if the upper limit of the confidence interval will be below the non-inferiority margin of 4 points. Amitriptyline will be declared non-inferior to CBT-I if the upper bound of the 95% confidence interval does not exceed the non-inferiority margin of 4 points. If amitriptyline is shown to be non-inferior, we then will proceed to superiority hypothesis testing. For superiority testing, we will consider the two sided 95% confidence interval of the mean difference between both groups on the primary outcome as established in the ANCOVA and verify if it includes zero or not.

The primary analysis will be conducted according to intention-to-treat, i.e., all randomized patients are included and are analyzed in their randomly assigned treatment group. We will use multiple imputations to handle missing data for outcomes that are based on the measurement at a single time point, including the primary outcome of the ISI score at week 12. We will include all baseline demographic and clinical characteristics in the imputation model. We will impute a total of five datasets and these will be pooled according to Rubin’s rule [63].

Additionally, the mean ISI score over time will be compared between the two treatment groups using linear mixed models with treatment group (amitriptyline or CBT-I) and time (6 and 12 weeks from baseline) included as fixed effects and ISI score at baseline included as covariate.

We will repeat the ANCOVA and the linear mixed models analysis of the ISI score as a per protocol analysis in which only patients who actually received their assigned treatment (in the CBT-I group attendance of at least 5 out of 7 sessions and in the AM group at least 70 out of 84 days medication) will be included.

Percentages responders until relapse at 2, 4, 6, 8, 10, and 12 months post treatment in both treatment groups will be compared using survival analyses. We will express the difference between amitriptyline and CBT-I in effect sizes and percentage responders. Treatment response is defined as ≥ 8 point reduction on ISI. A relapse is defined as a drawback of ≤ 8 points to the baseline score of the Insomnia Severity Index measured during follow-up at two subsequent measurements.

ANCOVA will be repeated on the secondary outcome measures assessed at week 12 and 12 months, adjusted for the baseline measurement and the linear mixed models will be repeated for the secondary outcomes sleep quality, fatigue, emotional complaints, physical functioning, impairment of functioning, and pain, all assessed at weeks 6 and 12 and 12 months post treatment adjusted for the baseline measurement, according to intention to treat and per protocol analyses. Bonferroni corrections will be applied to the p-values to account for multiple comparisons.

Rates of reported side effects, withdrawal, and rebound symptoms as well as the treatment evaluation items will be described.

The demographic characteristics will be used to identify potential subgroups. Moderators (data on demographic variables, type of insomnia, treatment preference) will be investigated to see whether these factors influence the intervention’s effectiveness (power of the analyses permitting). We will explore the extent to which these variables moderate the effect of the interventions by including interaction terms between these variables on the one hand and intervention type on the other hand in the ANCOVAs.

Mediation analysis will be conducted to explore the possible underlying mechanisms of the level of reduction in subjective insomnia after amitriptyline or CBT-I at week 12. We will perform multiple mediation analysis using bootstrapping to test the mediating effect of the potential mediators (pre sleep arousal and dysfunctional cognitions and beliefs about sleep).

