### Randomization and blinding

When the baseline questionnaires and the sleep diary are completed, the participants are randomized. Randomization is computer generated, by the webbased system (CastorEdc). Block randomization (blocks of 2 or 4) will be used to create similar distributions in the different study arms. Randomization into the two treatment groups is at patient level and will be stratified by benzodiazepine use, at least once every 2 weeks (i.e., no *versus* benzodiazepine use) at baseline and by referral type (self-referral versus referral by health care worker). Randomization will be executed centrally by a researcher/assistant who is not involved in the recruitment and inclusion of patients.

The research assistant informs the participants by phone about the result of the randomization procedure and explains the CBT-I appointment or how to collect the medication at the hospital pharmacy. The coordinating researcher and participant agree upon and document the date on which the participant will start taking/attending the study treatment.

It is not possible to blind participants or therapists to allocation; statistical analysis will be conducted by an independent statistician who will be blinded for group allocation.

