## Interventions

### Medication

The treatment regime for the low dose of AM mimics current off-label practice as much as possible, i.e., a 12-week period of 10 mg AM, with the possibility of doubling the dosages by patients themselves at approximately 3 weeks, and medication stop at 12 weeks. Furthermore, participants who opt for a double dosage regime are allowed to return to a single dosage regime within the 12 week treatment. The participants in the AM group have a consultation with a neurologist at least once during treatment at approximately 6 weeks and at 12 weeks to evaluate the effect, dosage, and side-effects of treatment and guide medication stop. At the 6 weeks consultation, participants who doubled their dose to 20 mg at 3 weeks and wish to continue this double dose up to 12 weeks will receive prescription for a second badge AM as one badge AM is only sufficient for a single dose for 12 weeks. The neurologist inquires and motivates the adherence to medication during the appointment at 6 weeks after start of treatment. At the 12 weeks consultation, the neurologists motivate and guide medication stop.

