### CBT-I

CBT-I consists of 6 weekly group sessions and a follow-up session at 12 weeks with a psychologist, specialized in insomnia and medical psychology. The treatment protocol is the manual of Verbeek et al. [43], and treatment elements are as follows: psycho-education, sleep hygiene, relaxation, behavior techniques such as stimulus control and sleep restriction, cognitive interventions, and relapse prevention. The degree of application of the behavioral techniques and sleep restriction is adapted to the medical condition (e.g., caution is advised with balance problems). If due to measures, for instance in the context of the COVID-19 pandemic, the group treatment cannot be offered face to face, the treatment will be offered by videoconferencing in group or individually via a secured connection. The psychologist inquires and stimulates adherence to CBT-I every session.

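### CBT-I is delivered in therapy groups, but the primary ANCOVA treats all patients as independent, so both primary tests run somewhat above their nominal error level

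*Protocol article*

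**What the plan says.** Allocation is individual: "Randomization into the two treatment groups is at patient level" (Randomization and blinding), "both for a period of 12 weeks in a ratio of 1:1" (Methods/design).

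The arms differ in how treatment is delivered. Under CBT-I: "CBT-I consists of 6 weekly group sessions and a follow-up session at 12 weeks with a psychologist, specialized in insomnia and medical psychology". If face-to-face groups are impossible, "the treatment will be offered by videoconferencing in group or individually via a secured connection". Under Medication, amitriptyline is taken by each patient alone: "The participants in the AM group have a consultation with a neurologist at least once during treatment at approximately 6 weeks and at 12 weeks".

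Statistical analysis sets the primary model for week-12 ISI as "analysis of covariance (ANCOVA) with treatment group (amitriptyline or CBT-I) as the independent variable and the baseline value as a covariate". This one ANCOVA supplies the one-sided 95% interval compared with the 4-point margin and, if non-inferiority is shown, the two-sided 95% interval for superiority. The section lists the ANCOVA assumptions to be checked as "normality, homogeneity of variance and random independent samples", and gives no action if one of them fails. The Sample size section mentions neither an ICC nor a design effect.

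**The concern.** Patients in one CBT-I group share sessions, a psychologist and each other's company for the length of the course, so their week-12 scores may resemble each other more than those of patients from different groups. Amitriptyline patients have no such shared treatment. The design is therefore partially nested: clustered in one arm, independent in the other.

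The ANCOVA estimates its standard error as if all patients were independent. With a positive within-group correlation the CBT-I mean is less precise than the model reports. The upper confidence limit then sits too low and falls under the margin too often. Both primary decisions, non-inferiority and then superiority, rest on this one standard error.

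**Working it through.** **Inputs from the protocol article.** SD 4.4, margin 4, one-sided 5%, 84 per group (Sample size); 1:1 allocation (Methods/design); ANCOVA with treatment and baseline only (Statistical analysis).

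**Inputs assumed, because the article does not give them.** Trial patients per therapy group, m = 2 to 8; ICC = 0.01 to 0.10.

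**The plan's own sample size.** The usual formula, n = 2 × [4.4 × (1.645 + 1.282) / 4]², gives 21 per group, not 84. A distance of 2 points gives 83 (84 with the t distribution). This gap is a separate matter. It matters here only because 84 per group is far more than margin 4 and SD 4.4 require.

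**Formulas.**
- Design effect in the CBT-I arm: DE = 1 + (m − 1) × ICC.
- Naive SE = 4.4 × √(2/84) = 0.679.
- True SE = 4.4 × √[(1 + DE)/84].
- Ratio naive/true = √[2/(1 + DE)]; it does not depend on the SD.
- True one-sided level = 1 − Φ(1.645 × ratio); true two-sided level = 2 × [1 − Φ(1.960 × ratio)].

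**Results.**

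| m | ICC | DE | True SE | Naive SE too small by | One-sided level | Two-sided level |
|---|---|---|---|---|---|---|
| 2 | 0.01 | 1.01 | 0.681 | 0.2% | 5.0% | 5.1% |
| 2 | 0.10 | 1.10 | 0.696 | 2.4% | 5.4% | 5.6% |
| 4 | 0.05 | 1.15 | 0.704 | 3.6% | 5.6% | 5.9% |
| 4 | 0.10 | 1.30 | 0.728 | 6.7% | 6.3% | 6.8% |
| 6 | 0.05 | 1.25 | 0.720 | 5.7% | 6.1% | 6.5% |
| 6 | 0.10 | 1.50 | 0.759 | 10.6% | 7.1% | 8.0% |
| 8 | 0.10 | 1.70 | 0.789 | 13.9% | 7.8% | 9.2% |

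**Simulation check.** With 84 per arm, a true difference of 4 and a two-group comparison ignoring clustering, the one-sided error was 5.0% at ICC 0, 6.2% at m = 6 and ICC 0.05, and 7.2% at m = 6 and ICC 0.10. The formula gives 5.0%, 6.1% and 7.1%.

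**Effect on the decision.** The naive rule declares non-inferiority when the observed difference is below 4 − 1.645 × 0.679 = 2.88 points. With the true SE the cut-off is 2.82 at m = 6 and ICC 0.05, and 4 − 1.645 × 0.789 = 2.70 at m = 8 and ICC 0.10.

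**Power.** At margin 4 with no true difference, DE 1.7 and a correct SE, power = Φ(4/0.789 − 1.645) = Φ(3.43), about 99.97%.

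**The case against.** Five arguments on the other side deserve weight.

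**The clusters may be small.** Trial status reports 68 randomized at submission, so about 34 to CBT-I. Recruitment began in September 2019 and a fourth hospital joined in June 2021, at least about 21 months: 34/21 ≈ 1.6 CBT-I patients per month over one to four hospitals. At that pace 6 to 8 trial patients would take roughly 4 to 5 months to gather, even at one site. The trial runs within regular care, so groups may also include non-trial patients, though that is inference. Individual videoconferencing is allowed as a fallback, and patients treated that way add no group clustering. This stands. It is why the range starts at 2 per group; at 2 to 4 per group the one-sided level is only about 5.0% to 6.3%.

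**The verdict would rarely change.** This also stands. Even at m = 8 and ICC 0.10, only an estimate between 2.70 and 2.88 would be decided differently.

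**Independence is to be checked.** This does not answer the point. The grouping is known in advance, the check has no stated consequence, and a known feature of delivery belongs in the model.

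**The full protocol or SAP may deal with it.** The article is silent on the random effects of its linear mixed models, and that silence is no evidence of an omission there. The primary ANCOVA is different: its terms are spelled out, and they do not fit the delivery described.

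**Leaving out the stratification factors tends to make the standard error slightly too large.** That could offset a very small ICC, but it is no substitute for modelling the clustering.

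A reader might also infer that the trial loses its stated 90% power. The article's figures do not support that: at margin 4, SD 4.4 and 84 per group, power stays above 99.9% throughout the range. A material loss appears only if the trial was sized for a 2-point distance, which the article nowhere states.

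**Conclusion.** The point holds as a mismatch between how CBT-I is delivered and the model that carries the primary decision. The direction is certain for any positive within-group correlation; the size is not, because the article gives neither ICC nor group size. Under the assumed 2 to 8 trial patients per group and ICC 0.01 to 0.10, the standard error is about 0% to 14% too small, the one-sided level is about 5.0% to 7.8% and the two-sided level about 5.1% to 9.2%. The figures assume equal group sizes and all CBT-I patients treated in groups; individual delivery would shrink them. This is worth correcting because the remedy is cheap and the non-inferiority claim depends on its error rate, but it does not threaten the trial.

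**What to change.** Record a therapy-group identifier for every CBT-I patient. Recruitment was ongoing at submission, with 68 of 190 randomized, so this can start now and be rebuilt from session records for earlier patients where those exist.

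Replace the plain ANCOVA as the source of the primary confidence interval by a partially nested mixed model:
- fixed effects for treatment and baseline ISI;
- a random intercept for therapy group in the CBT-I arm only;
- CBT-I patients treated individually, or who never joined a group, kept in the intention-to-treat analysis as clusters of one;
- small-sample degrees of freedom (Kenward-Roger or Satterthwaite).

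A cluster-robust standard error around the existing ANCOVA is an acceptable alternative.

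Make the same allowance in the per-protocol and repeated-measures analyses. Make the planned multiple imputation consistent with it: the imputation model should reflect therapy group, and the plan should say how the small-sample degrees of freedom are combined with Rubin's rules across the five datasets.

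The cost is one extra data item, a slightly wider confidence interval and a little more analysis work. No treatment, visit or endpoint changes.

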## Assessments and outcomes

### Timing of assessments

Participants will be recruited from September 2019 to December 2022. They will be assessed at baseline (pre-randomization), 3, 6, and 12 weeks (end of treatment). Follow-up assessments will take place at 2 weeks, and at 2, 4, 6, 8, 10, and 12 months post treatment.

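### The stated imputation model for week 12 ISI names only baseline variables; followed literally, without arm, it pulls the arms together and raises false non-inferiority at the margin from 5% to about 17%

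*Protocol article*

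**What the plan says.** The Statistical analysis section of the protocol article sorts outcomes into two routes.

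- Outcomes measured at weeks 6 and 12 go to mixed models, on the ground that "Mixed linear models can handle the presence of missing data without the need for imputation".
- Multiple imputation is used "for outcomes that are based on the measurement at a single time point, including the primary outcome of the ISI score at week 12", with five datasets pooled by Rubin's rule. The content of the imputation model is then given: "We will include all baseline demographic and clinical characteristics in the imputation model".

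The primary test is an ANCOVA of week 12 ISI on treatment group and baseline ISI. The next paragraph adds a mixed model of the ISI at weeks 6 and 12, so a week 6 ISI exists. The Timing of assessments section also lists a week 3 visit, without saying which instruments are used then.

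The decision rule is one-sided: "We will calculate a one-sided 95% confidence interval around the mean difference in the primary outcome". The upper limit is compared with a margin of 4 points.

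**The concern.** The article chooses to state the predictors, and the ones it states are all baseline variables. Randomised arm is not a baseline characteristic, and randomisation makes it independent of them, so no set of baseline variables can stand in for it. If arm is absent, missing week 12 scores in both arms are drawn from the same distribution given baseline, and the imputed patients contribute a treatment difference of about zero.

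In a superiority trial that dilution is conservative. Here it moves the estimate away from the margin and towards the claim, in the analysis that decides the trial.

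A second, separate question is why week 12 ISI is handled as a single-time-point outcome when the same scale is modelled at week 6. A patient with a recorded week 6 score but no week 12 score would be imputed as if the week 6 score were unknown.

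**Working it through.** **Inputs from the article.** Margin: the mean post-treatment ISI on amitriptyline "does not exceed that of the CBT-I group by more than 4 points". SD 4.4, dropout 13% and 190 participants (Sample size); 1:1 allocation (Methods/design), so 95 per arm. One-sided 5% test, ANCOVA with baseline ISI, five imputations, Rubin's rule (Sample size, Statistical analysis).

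**Assumptions not in the article.** Correlations: baseline with week 12 ISI 0.4, baseline with week 6 0.45, week 6 with week 12 0.65. The week 6 difference is 75% of the week 12 difference. Every dropout lacks the week 12 ISI. Baseline ISI stands for the baseline characteristics.

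**The plan's own figure.** The article gives no figure for the imputation; its only design calculation is the sample size. With margin 4 and SD 4.4, n = 2 × [(1.645 + 1.282) × 4.4 / 4]² = 20.7, so 21 per arm, not 84. A 2-point distance gives 82.9, so 83 (84 with the noncentral t). The total follows from 84 × 2 × 1.13 = 189.8, i.e. 190. This mismatch is a separate matter. The check below uses the stated 190.

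**Step 1, attenuation by arithmetic.** Let a fraction f be missing completely at random in each arm. Observed patients carry the true difference D, and patients imputed without arm carry about 0. The expected estimate is (1 − f) × D + f × 0 = (1 − f) × D. With D = 4 and f = 0.13 this is 4 × 0.87 = 3.48.

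**Step 2, simulation at the boundary.** True difference 4 (the margin), 2000 trials per setting, five imputations. False non-inferiority is the share of trials whose upper one-sided 95% limit lies below 4.

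| Missing | (1 − f) × 4 | Baseline only: mean estimate | Baseline only: false non-inferiority | Baseline + arm: mean estimate | Baseline + arm: false non-inferiority |
|---|---|---|---|---|---|
| 5% | 3.80 | 3.79 | 8.2% | 3.99 | 5.30% |
| 13% | 3.48 | 3.49 | 16.9% | 4.02 | 4.50% |
| 20% | 3.20 | 3.21 | 26.6% | 4.01 | 4.55% |
| 30% | 2.80 | 2.80 | 47.5% | 4.02 | 4.45% |

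The Monte Carlo standard error is √(0.169 × 0.831 / 2000) = 0.8 percentage points at 16.9%, and √(0.05 × 0.95 / 2000) = 0.5 points at 5%. Two further simulations of the 13% setting gave 17.2% and 17.6%, each with a mean estimate of 3.46.

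**Step 3, the two omissions separated** (13% missing, true difference 4).

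- Missing completely at random: baseline + week 6 ISI without arm gives 3.76 and 8.75%; baseline + arm + week 6 ISI gives 4.01 and 5.1%.
- Missingness depending on week 6 ISI (base rate about 13%): baseline only 3.40 and 19.3%; baseline + arm 3.94 and 6.55%; baseline + arm + week 6 ISI 4.00 and 5.25%. A further run gave 5.8% without and 4.6% with week 6 ISI, arm being included in both.

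The pull between the arms therefore comes from leaving out arm. Week 6 ISI recovers only part of it by itself. Once arm is in, adding week 6 ISI changes the error rate by about one percentage point, and only when missingness depends on it.

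**Step 4, sensitivity.** With a baseline correlation of 0.6 (week 6 with week 12 at 0.7), baseline-only imputation gives 17.9%. With 16% missing under CBT-I and 10% under amitriptyline it gives about 17.3%. With a true difference of 0 the mean estimate is −0.001, so there is no bias.

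**The case against.** The strongest reply is that the sentence lists what goes in and shuts nothing out. It does not say *only*. It can be read as adding auxiliary variables to those already in the ANCOVA, namely arm and baseline ISI. A journal article also condenses a full protocol, and the complete predictor list may stand there or in a SAP. This stands in part: the omission of arm is the literal reading, not an explicit exclusion, and the error rates above hold only if arm is in fact left out. But the article is not silent on the model's content, and it names treatment group in its other models (ANCOVA, mixed model, moderator interactions).

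Several stronger readings are tempting and are not supported.

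- A reader might infer that the plan excludes arm. It does not say so.
- A reader might hold that omitting on-treatment ISI also pulls the arms together. Step 3 shows that, with arm included, it does not under missingness completely at random and does so only slightly otherwise.
- A reader might assume that a week 3 ISI is being discarded. The text does not say that the ISI is taken at week 3, and the schedule figure is not shown.
- A reader might suspect that baseline ISI is left out, because it is listed apart from clinical characteristics. That listing concerns what will be tabulated, and baseline ISI is the ANCOVA covariate.
- A reader might blame the five imputations. With arm included, five give 4.5%.

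The additional mixed model needs no imputation and offers a partial cross-check. It is not the analysis from which non-inferiority is declared. Nor is agreement of the per-protocol analysis stated as a condition.

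**Conclusion.** The point holds in a conditional form. As worded, the imputation model for the primary outcome names baseline variables alone. Carried out that way, at the plan's 13% dropout, the estimate at the margin falls from 4 to about 3.5 points and the one-sided error rises from 5% to about 17%. The direction favours the trial's claim.

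The attenuation is close to pure arithmetic. The error rate rests on SD 4.4, 95 per arm, an assumed baseline correlation of 0.4 (to which it is not sensitive), data missing completely at random and all dropouts lacking the week 12 score. The bias is proportional to the true difference and vanishes at 0, but error control for non-inferiority is judged at the margin.

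Leaving out week 6 ISI is a lesser, separate weakness. It loses information, makes the missing-at-random assumption less plausible, and adds only a small bias once arm is included.

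**What to change.** Replace the sentence on the imputation model with one that says week 12 ISI is imputed separately by arm, or with arm in the model. The predictors should be baseline ISI, on-treatment ISI (week 6, and week 3 if the ISI is collected then), the two stratification factors (benzodiazepine use and referral type) and the baseline characteristics.

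The cost is a line of wording and trivial computing time. The week 6 ISI is already planned, so no new data are needed. If the full protocol or SAP already includes arm and week 6 ISI, it is enough to align this text with it before the data are analysed. A larger number of imputations, or a mixed model as the primary analysis, would be a matter of preference and is not needed to remove this error.
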